## II. Background and Significance:

### 1.0 Significance

### 1.1 African Americans have a higher prevalence of uncontrolled hypertension than white Americans leading to disparities in cardiovascular outcomes.

One in 3 US adults has hypertension and African Americans are disproportionately affected; almost 40% of non-Hispanic blacks have hypertension. Although the rates of uncontrolled hypertension have been decreasing in all groups, African Americans continue to have higher rates of uncontrolled hypertension compared to white Americans. Uncontrolled hypertension disproportionately affects outcomes in African Americans compared to whites. A 10-mm Hg difference in systolic blood pressure (SBP) is associated with an 8% increase in stroke risk for whites, but a 24% increase in risk for African Americans. Lower adherence to treatment recommendations may contribute to higher rates of uncontrolled hypertension among African Americans. Therefore, interventions to improve adherence have the potential to reduce racial disparities in hypertension outcomes.

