### 1.3 Stereotype threat may contribute to low adherence.

Stereotype threat occurs when cues in the environment (such as visiting a doctor's office) trigger the threat of confirming, as self-characteristic, a negative stereotype about one's group. Although any individual may experience stereotype threat, African Americans are at greater risk due to widespread racism and past experiences of discrimination. In the clinical setting, African American patients report stereotype threat related to being viewed as unintelligent, "second class citizens", and unworthy of good care.

Stereotype threat triggers psychological and physiological responses including reduced memory capacity, impaired communication, disengagement and reduced motivation. Stereotype threat may thus contribute to racial disparities in non-adherence to treatment by hindering a patient's ability to process information and actively engage in a discussion about their health during a clinical encounter. Based on this poor clinical interaction, the patient may feel less activated to adhere to treatment recommendations. Therefore, interventions targeting stereotype threat have the potential to reduce disparities among populations that experience widespread discrimination. (Figure 1)

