### C. Study Design and Research Methods

[figure not shown]

**Overview:** The study design was developed in consultation with providers at the study sites to ensure feasibility of implementation in routine clinical practice. All primary care providers (PCP) at the participating clinics will be invited to complete a baseline survey regarding past disparities training and racial attitudes; patient participation will be independent of whether their PCP

participates. We will enroll self-identified African American and white patients with uncontrolled hypertension who are eligible and consent for the study. Our primary outcome is medication adherence that will be measured in three ways: 1) pharmacy fills, 2) self-report, and 3) pill counts. At the index visit, before they see their PCP, participants will have their blood pressure recorded and will complete a survey which includes a validated self-report measure of adherence (see Table 1 for survey contents). We will also query the EHR for baseline adherence based on prior 12-months pharmacy fills. Participants will be randomized to the values affirmation or control intervention tasks and they will complete the assigned task before seeing their PCP as scheduled. Following the visit, patients will complete a brief survey. Participants will return at 3-months and 6-months for in-person follow-up visits that will include assessment of adherence, blood pressure measurement and completion of surveys. Participants will be asked to bring all antihypertensive medications to each follow-up visit, and fill date and number of pills in the bottle will be recorded. Adherence will be calculated for each antihypertensive drug in the regimen and combined across drugs into a summary measure of adherence for the entire drug regimen. Secondary outcomes include blood pressure, time under blood pressure control, and appropriate treatment intensification. Throughout the study, we will evaluate the intervention for widespread dissemination based on the RE-AIM framework.

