The primary outcome variable (adherence measured by pharmacy refills) is continuous; in the event that normality assumptions are not met we will use transformations to normalize distributions. For the primary comparisons, we will employ intent-to-treat analyses, although we expect few or none of the randomized patients to not complete an exercise. We will examine overall values affirmation effectiveness between the racial groups. We will next create models with adherence as the dependent variable including the potential moderator variable (prior experience of discrimination) then including the potential mediator variables (patient activation, attitude, social norms, perceived behavioral control, and anticipated emotion). Finally, we will explore whether the collected provider variables (racial bias, past cultural competency training, self-efficacy and racial mix of clinical site) moderate the relationships. We will also include patient gender and provider race as a possible moderating variables. We will use general (or generalized, for dichotomous outcomes) linear mixed models, examining alternative structures for the variance-covariance matrix for the level 1 model by comparing goodness of fit for the different models as well as model fitting diagnostics to assess for influential points, outliers, overdispersion and heteroscedasticity. We will employ methods that utilize all available data, assuming ignorable missingness.

In secondary analysis using the self-reported adherence measures, we will dichotomize the groups into non-adherent (score  $\geq 2$  on any "extent" item) and adherent. We will also compare the pill count measure of adherence to the pharmacy fill estimates of adherence for validation. For blood pressure, the secondary outcome, we will compare the index and follow-up visits using mixed effects repeated measures models with a patient random effect. All hypothesis tests will be two-sided with  $\alpha=.05$ . Statistical analysis will use SAS 9.4.

**Statistical Model for Primary Outcomes.** The structure of the data is hierarchical (patients nested within providers) and longitudinal (repeated measures on patients over time). Baseline (time 0) is defined as the adherence rate for the 12-months prior to the index visit.

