3. Racial differences in values and qualitative themes: We will use quantitative Poisson regression models and qualitative content analysis to determine the frequency of values chosen during the values affirmation writing exercise and identify common qualitative themes for why each value was chosen among racial groups.
  4. Past experiences of discrimination and uncontrolled blood pressure: We will determine whether there is an association between past experiences of discrimination and the degree of uncontrolled blood pressure at patients' index visit. If so, we will examine potential moderators of that relationship (satisfaction with clinician, patient activation, attitudes toward blood pressure control) while controlling for socioeconomic status and treatment variables.
  5. Pill management strategies and pill count adherence: To investigate how strategies used by patients to manage their medications outside the clinic are associated with adherence to medications, we will describe the self-reported frequency of strategies used by patients to manage their pills at home. The association between each strategy and patients' pill count adherence (proportion of actual over expected pills taken) will be determined at each study timepoint. In secondary analyses, the strategies associated with apparent outliers will be examined at the baseline visit.
  6. Factors contributing to the racial disparity in antihypertensive medication adherence: To assess whether racial disparities in medication adherence can be explained by pre-specified covariates, we will use the Oaxaca-Blinder decomposition method. We will determine general sample characteristics of the patient population who are adherent and non-adherent to antihypertensive medications, determine the overall disparity in medication adherence between White and Black patients explained by covariates, and then calculate the contribution each covariate to the disparity in medication adherence by race. Pre-specified covariates will include those already collected during the study (demographics, clinical factors, medication use, health care utilization, perceived discrimination, attitudinal factors, and behavioral factors). **UCD will share a de-identified data set with one of our subcontractors (Kaiser Permanente Mid-Atlantic States), and they will conduct these analyses on site.**

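### Additional analysis 4 relates discrimination to index-visit blood pressure in a two-race sample without naming race as a covariate, so the association could arise from race alone (low severity)

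*Protocol*

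**What the plan says.** Protocol, section F (Data Analysis Plan), additional analysis 4, has two steps.

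- **Step 1:** "We will determine whether there is an association between past experiences of discrimination and the degree of uncontrolled blood pressure at patients' index visit". No covariate is attached to this sentence.
- **Step 2:** "If so, we will examine potential moderators of that relationship". The moderators listed are "satisfaction with clinician, patient activation, attitudes toward blood pressure control", and the step is carried out "while controlling for socioeconomic status and treatment variables".

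Race is in neither list, and nothing restricts or stratifies the analysis by race. The sample contains both groups by design (section C): "We will enroll self-identified African American and white patients with uncontrolled hypertension who are eligible and consent for the study". Section F plans 480 of each race before allowance for attrition.

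The background ties race to both sides of the relationship. On exposure, section 1.3 says "African Americans are at greater risk due to widespread racism and past experiences of discrimination". On outcome, section 1.1 says "African Americans continue to have higher rates of uncontrolled hypertension compared to white Americans".

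**The concern.** On the protocol's own premises, race is a common correlate of the exposure and the outcome. If African American patients report more discrimination and also have higher index-visit blood pressure, the two variables will correlate in the combined sample even when they are unrelated within each race. A test without a race term cannot separate that from a relationship between discrimination and blood pressure among patients of the same race.

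Additional analyses 1, 2, 3 and 6 in the same list all bring race or racial group in explicitly. Analysis 4 does not, although its exposure and outcome are both tied to race. The protocol says results from this list will go into abstracts and manuscripts. A reported association that only restates the racial difference in blood pressure would be easy to misread, on the very subject the trial addresses.

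**Working it through.** Analysis 4 states no sample size, power or effect size, so it has no figure of its own to reproduce. The check borrows inputs from elsewhere in section F and adds assumptions where the protocol gives nothing.

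**Inputs from the protocol**

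- Enrolled sample: 960/(1 - 0.15) = 1,129.4, rounded up to 1,130. This reproduces the stated total.
- 240 per cell and an effect size of 0.26 SD give 81% power by a two-sample calculation, against the stated 80%.
- Significance level 0.05: "All hypothesis tests will be two-sided with" that level.
- Systolic SD, which is not stated. It is implied by the 4.7 mmHg difference said to be detectable between cells with 80% power: 4.7/[(1.96 + 0.842) × √(2/240)] = 4.7/0.2558 = 18.4 mmHg.

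**Assumptions**

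- The 1,130 patients split evenly by race, as the planned 480 and 480 suggest.
- Discrimination and systolic pressure are unrelated within each race.
- The races differ by d1 = 0.25, 0.5 or 1.0 SD in discrimination score.
- The races differ by 2, 4 or 6 mmHg in index systolic pressure, so d2 = 2/18.4, 4/18.4 or 6/18.4 = 0.109, 0.217 or 0.326 SD.

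**Closed form.** With an even split, the correlation induced by race alone is

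r = [d1/√(d1² + 4)] × [d2/√(d2² + 4)],

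and Fisher's z has standard error 1/√1127. Worked example with d1 = 1.0 and d2 = 0.326:

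- r = 0.447 × 0.161 = 0.072
- expected z statistic = 0.072 × √1127 = 2.42
- chance of exceeding 1.96 in absolute value = 68%

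**Simulation.** Linear regression was run 2,000 times per setting, with and without a race term. The table gives the chance that step 1 is positive with no race term.

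| Discrimination gap | SBP gap 2 mmHg | 4 mmHg | 6 mmHg |
|---|---|---|---|
| 0.25 SD | 5% | 8% | 10% |
| 0.5 SD | 7% | 14% | 26% |
| 1.0 SD | 12% | 36% | 67% |

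The closed form agrees to within about one percentage point in every cell: 6/7/10%, 7/14/26% and 13/37/68%. With race in the model, the simulated rate is 4-6% throughout, which is the nominal 5% within simulation error.

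**The condition on step 2.** Suppose the correlation is 0.10 in one half of the sample and 0 in the other.

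- Step 1 sees an average of about 0.05. Its expected z is 0.05 × √1127 = 1.68, so it passes 39% of the time.
- The interaction test run without the condition compares two halves of 565. Its expected z is 0.1003/√(2/562) = 1.68, so its power is also 39%.

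If the correlations are instead +0.10 and -0.10, step 1 passes 5% of the time and the interaction test has 92% power. That contrast requires an exact reversal of sign.

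**The case against.** The strongest reply is that item 4 is two sentences in a list of exploratory analyses. It gives no model, and its control classes are broad. Age and sex are not named either, and nobody would conclude that they are barred. A statistical analysis plan could add race, and nothing in item 4 prevents it. This stands in part: the protocol does not exclude race, and analysis across both races is inferred from the absence of any restriction. But the protocol does name a control set and a moderator list for this question, and followed as written neither contains the one variable that its own background ties to both exposure and outcome.

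Second, the premise for a blood pressure gap is weaker here than in the general population. Section 1.1 concerns rates of uncontrolled hypertension. The trial admits only patients with a reading of at least 140/90 mmHg in the preceding 12 months, which may narrow the gap at the index visit. Socioeconomic adjustment, if also applied to step 1, could absorb part of what remains. Both points stand, and they are why small gaps belong in the range.

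Third, a reader might infer two stronger criticisms that the document does not support.

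- **That the condition on step 2 is an error.** Examining moderators only after finding an association is a defensible restraint on multiple exploratory tests. In the 0.10-versus-0 case the unconditional interaction test does no better than the condition, and nothing in the protocol suggests the sign reversal needed for the 5%-versus-92% contrast.
- **That the plan would present the race gap as an effect of discrimination.** Item 4 speaks only of an association.

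**Conclusion.** The point holds for the missing race term. As written, step 1 has no stated adjustment and step 2 controls only for socioeconomic status and treatment, so an association could be found with none present within either race.

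The size depends on two gaps that the protocol does not give. The excess over 5% is negligible to small at a 0.25 SD discrimination gap (about 5-10%). It becomes substantial only when a gap of 0.5-1.0 SD is combined with a systolic gap towards the upper end of 2-6 mmHg; the full range there is about 7-67%. These figures also assume an even race split, no attenuation from other covariates, and the implied SD of 18.4 mmHg.

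Severity is low. The analysis is exploratory, serves none of H1 to H4, and cannot alter the primary or secondary results.

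**What to change.** In additional analysis 4, name race as a covariate in both the association step and the moderator step, include a discrimination by race term, and report the slope of blood pressure on discrimination within each race.

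Race and the discrimination score are already collected at baseline, so no new data are needed. The cost is two terms in one exploratory model and two reported slopes instead of one, with the lower precision of race-specific estimates.

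Removing the condition on the moderator step is optional. It would allow moderation to be seen when the average slope is near zero, at the price of more exploratory tests to report.

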#### **G. Summarize Knowledge to be Gained:**

Potential benefits of the proposed research to the subjects and others: Benefit from participating in the research cannot be claimed. If, however, the intervention being studied is effective, subjects randomized to the experimental group may experience improvements in blood pressure control and other parameters dependent on uptake of self-management skills. Given the magnitude of the problem of race-based health disparities, the potential of the proposed intervention to reduce these disparities, and the minimal risk to subjects, we are of the opinion that the risk-benefit ratio for this study is favorable.

Importance of the knowledge to be gained: Our preliminary data suggest the intervention will be effective. The current study is designed to generate knowledge that will justify widespread adoption if effectiveness is demonstrated. Because virtually no interventions to improve relationships between physicians and minority patients have been reported, a positive result of this study might have widespread clinical applicability. We also seek data on the potential for this social psychology intervention to have direct effect on blood pressure.

**IN SUMMARY**, our proposed study moves beyond documentation of race-based health disparities and towards an effective intervention. We focus on a medical condition – hypertension – that is arguably the single greatest contributor to mortality disparities for African

Americans. Our pilot data suggest a values-affirmation intervention improves patient-provider communication, which in turn improves subsequent medication adherence. Our pilot studies, however, leave gaps in knowledge that we propose to answer to determine the effectiveness of using values affirmation as a means of reducing racial disparities in health care. If successful, this study will be the first to provide evidence for a low-resource intervention that has the potential to substantially reduce healthcare disparities across a wide range of health care conditions and populations.

